## Abstract

**Introduction:**

We previously assessed the effect of an onsite sanitation intervention in informal neighbourhoods of urban Maputo, Mozambique on enteric pathogen detection in children after 2 years of follow-up (Maputo Sanitation (MapSan) trial, ClinicalTrials.gov: NCT02362932). We found significant reductions in *Shigella* and *Trichuris* prevalence but only among children born after the intervention was delivered. In this study, we assess the health impacts of the sanitation intervention after 5 years among children born into study households postintervention.

**Methods and analysis:**

We are conducting a cross-sectional household study of enteric pathogen detection in child stool and the environment at compounds (household clusters sharing sanitation and outdoor living space) that received the pour-flush toilet and septic tank intervention at least 5 years prior or meet the original criteria for trial control sites. We are enrolling at least 400 children (ages 29 days to 60 months) in each treatment arm. Our primary outcome is the prevalence of 22 bacterial, protozoan, and soil transmitted helminth enteric pathogens in child stool using the pooled prevalence ratio across the outcome set to assess the overall intervention effect. Secondary outcomes include the individual pathogen detection prevalence and gene copy density of 27 enteric pathogens (including viruses); mean height-for-age, weight-for-age, and weight-for-height z-scores; prevalence of stunting, underweight, and wasting; and the 7-day period prevalence of caregiver-reported diarrhoea. All analyses are adjusted for prespecified covariates and examined for effect measure modification by age. Environmental samples from study households and the public domain are assessed for pathogens and faecal indicators to explore environmental exposures and monitor disease transmission.

**Ethics and dissemination:**

Study protocols have been reviewed and approved by human subjects review boards at the Ministry of Health, Republic of Mozambique and the University of North Carolina at Chapel Hill. Deidentified study data will be deposited at https://osf.io/e7pvk/.

**Trial registration number:**

ISRCTN86084138.

STRENGTHS AND LIMITATIONS OF THIS STUDYLong-term follow-up of an urban on-site sanitation intervention implemented at least 5 years prior so that all participants have been exposed to the treatment conditions for their entire lives.Primary study endpoint is molecular detection of multiple enteric pathogens in child stool, which unambiguously indicates previous exposure to specific sanitation-related pathogens.Primary outcome is the overall impact of the intervention on enteric pathogen exposure using a novel pooled estimate of the treatment effect across a prespecified set of enteric pathogens.As an observational evaluation of an existing intervention, sample size is constrained by the number of eligible children residing at study sites and selection bias arising from differential enteric pathogen-related mortality may be present, particularly among older age groups.As a cross-sectional study, there is potential for confounding bias in our estimates of the intervention impacts on child health, particularly as the intervention itself may have influenced the desirability of the intervention sites and thus the socioeconomic status of their residents, which may be associated with reduced pathogen exposures.

## Introduction

There is a high burden of childhood enteric infections associated with poor environmental conditions, with multiple enteric pathogens frequently detected in stool within the first year of life.^1–3^ This is also the period with the highest incidence of diarrhoea, which remains a leading cause of child mortality in low-income and middle-income countries and has long been associated with stunted growth.^4–6^ However, many diarrhoeal episodes are not attributable to infectious aetiologies,^3 7^ while the aetiology of attributable diarrhoea varies widely by setting and only certain diarrhoeal pathogens are consistently implicated in reduced linear growth.^2 8 9^ Far more prevalent is asymptomatic enteric pathogen shedding in stool,^3 7 10–14^ which may be more strongly associated with poor growth than diarrhoeal illness,^2 15–17^ potentially by contributing to intestinal inflammation, gut permeability, and nutrient malabsorption in a condition known as environmental enteric dysfunction (EED).^18–21^ In addition to the diverse negative impacts of stunting,^22^ specific adverse health outcomes associated with enteric infection and EED include delayed cognitive development^23–25^ and reduced oral vaccine efficacy.^26 27^

Water, sanitation and hygiene (WASH) interventions aim to prevent diarrhoea and improve child growth by interrupting faecal-oral pathogen transmission.^28^ However, recent rigorous WASH intervention trials have demonstrated inconsistent and often limited impacts on child health.^13 29–34^ Methodological limitations of the distal outcome measures used notwithstanding,^35 36^ these findings are consistent with the interventions insufficiently interrupting environmental transmission and exposure to enteric pathogens.^37^ Combined WASH interventions with high fidelity and adherence reduced stool-based detection of *Giardia*, hookworm and possibly *Ascaris* among 30-month-old children (but not younger children) and enteric viruses in rural Bangladesh,^10 38 39^
*Ascaris* in rural Kenya,^40^ and the number of codetected parasites in rural Zimbabwe,^11^ but not bacterial pathogens or those most associated with stunting in any setting.^2^ The sanitation-only intervention arm in rural Bangladesh reduced *Trichuris* prevalence in child stool^38^ and may have reduced pathogenic *Escherichia coli* on child hands in more crowded households,^41^ while a sanitation intervention in rural Cambodia did not impact any pathogens measured in child stool.^13^ Viewed collectively, a clear picture emerges of pervasive childhood polymicrobial exposures that were not meaningfully prevented by low-cost WASH interventions.^42–44^

The preceding trials were all conducted in rural settings, but rapid urbanisation has led to exceptional growth of densely populated informal settlements that lack basic services and present unique health challenges.^45 46^ We have previously investigated whether an onsite sanitation intervention delivered in low-income neighbourhoods of urban Maputo, Mozambique reduced enteric pathogen prevalence in child stool.^47^ Although we similarly found no evidence of an effect on combined prevalence of prespecified enteric pathogens in our primary analyses,^34^ additional evidence suggests that the sanitation intervention may have reduced exposures to enteric pathogens in the environment. The intervention was delivered with high fidelity and was widely used by intervention households after 2 years.^48^ Exploratory subgroup analyses indicated that 24 months after the intervention, *Shigella* prevalence was halved (−51%; 95% CI −15% to −72%) and *Trichuris* prevalence reduced by three-quarters (−76%; 95% CI −40% to −90%) among children born into the study compounds after the intervention was implemented, relative to children born into the control compounds after baseline.^34^ Furthermore, overall pathogen prevalence, pathogen counts, *E. coli* gene copy density, and the individual prevalence of *Ascaris* and pathogenic *E. coli* were all significantly reduced in soil at the intervention latrine entrance,^49 50^ suggesting the intervention effectively contained human excreta. While animals have been implicated as major sources of pathogen exposure in other settings,^51^ only companion animals were frequently present at study households and a locally validated indicator of poultry faecal contamination (the most commonly observed non-companion animal type) was rarely detected in household environments.^52^ Conversely, indicators of human faecal contamination were widespread^50^ and the two pathogens most impacted by the intervention—*Shigella* and *Trichuris*—are considered anthroponotic,^53^ suggesting that human excreta was a primary source of enteric pathogens in this dense, urban setting and that human-associated pathogens were impacted by sustained exposure to the intervention.

Enteric pathogen carriage is highly age-dependent,^8 12^ but we were previously limited by the timing of our follow-up survey (24 months postintervention) to children under 2 years of age when assessing impacts on those born into the intervention. Furthermore, it has been suggested that the typically short (1–2 years) follow-up periods often used in WASH evaluations may be inadequate for any longer-term benefits to manifest, potentially contributing to the limited observed effects.^42^ Accordingly, we are conducting a cross-sectional follow-up study to better understand the long-term impacts of the sanitation intervention 5 years after it was implemented on child enteric pathogen exposures and shedding, diarrhoeal disease, and growth among children born into study households postintervention.

## Study objectives

### Primary objective

To measure the long-term effect of a shared, onsite urban sanitation intervention on the pooled prevalence of prespecified enteric pathogen targets detected in children’s stool at least 60 months postintervention.

### Hypotheses

H1: The risk of stool-based enteric pathogen detection among children 29 days to 60 months old is reduced for children born into households that previously received the sanitation intervention.

H2: Children born into households that previously received the sanitation intervention experience delayed exposure to enteric pathogens relative to comparably aged children from non-intervention households, reflected in a greater reduction in the risk of enteric pathogen detection among younger age groups and attenuated reduction in risk among older children.

### Secondary objectives

To measure the effect of a shared, onsite urban sanitation intervention programme on the individual prevalence and density of prespecified enteric pathogen targets detected in children’s stool and environmental samples at least 60 months postintervention.To measure the effect of a shared, onsite urban sanitation intervention programme on child growth and the prevalence of caregiver-reported diarrhoea in children at least 60 months postintervention.

## Methods and analysis

### Study setting

This household-based study is being conducted in 11 bairros (neighbourhoods) in the Nhlamankulu district and 5 bairros in the KaMaxaquene district of Maputo city, Mozambique. Households in these densely populated, low-income neighbourhoods typically cluster into self-defined compounds delineated by a wall or boundary that share outdoor living space and sanitation facilities. Study activities with participating households are conducted primarily in the compound shared outdoor space by staff from the Centro de Investigação e Treino em Saúde da Polana Caniço (Polana Caniço Health Research and Training Centre; CISPOC) in Maputo, Mozambique, from which the study is implemented and managed.

### Study design

#### Urban sanitation intervention

The non-governmental organisation (NGO) water and sanitation for the urban poor (WSUP) implemented a sanitation intervention in 2015–2016 at approximately 300 compounds in informal urban neighbourhoods of Maputo under a larger programme led by the Water and Sanitation Programme of the World Bank.^47^ In these compounds, ranging between three and 25 households each, existing shared, unhygienic latrines were replaced with pour-flush toilets and a septic tank with a soak-away pit for the liquid effluent. Two intervention designs employing the same sanitation technology were implemented, with approximately 50 communal sanitation blocks (CSBs) and 250 shared latrines (SLs) constructed across 11 neighbourhoods that exhibited diversity across density and other key characteristics (susceptibility to flooding, relative poverty, access to water and sanitation infrastructure).^12 52 54^ SLs served compounds with fewer than 21 residents and provided a single cabin with the intervention toilet, while CSBs provided an additional cabin for every 20 compound residents and other amenities including rainwater harvesting, municipal water connections and storage, and washing, bathing and laundry facilities.^34 55^ WSUP also constructed facilities to the same specifications at other compounds in the neighbourhoods prior to 2015 and continued to deliver these intervention designs in the years following 2016.

#### Original controlled before-and-after study

To evaluate the impact of the WSUP sanitation intervention on child health, we conducted the Maputo Sanitation (MapSan) trial, a controlled before-and-after study of enteric pathogen detection in child stool (ClinicalTrials.gov: NCT02362932).^47^ WSUP selected intervention compounds using the following criteria: (1) residents shared sanitation in poor condition as determined by an engineer; (2) the compound was located in the predefined implementation neighbourhoods; (3) there were no fewer than 12 residents; (4) residents were willing to contribute financially to construction costs; (5) sufficient space was available for construction of the new facility; (6) the compound was accessible for transportation of construction materials and tank-emptying activities; (7) the compound had access to a legal piped water supply and (8) the groundwater level was deep enough for construction of a septic tank. Control compounds were selected according to criteria 1, 3, 4 and 7 from the 11 neighbourhoods where the intervention was implemented and 5 additional neighbourhoods with comparable characteristics.^12^

The MapSan trial recruited an open cohort at three time points: baseline (preintervention), 12 months postintervention, and 24 months postintervention; children were eligible to participate if older than 1 month at the time of enrolment and under 48 months at baseline. We enrolled intervention and control compounds concurrently to limit any differential effects of seasonality or other secular trends on the outcomes. We found no evidence that the sanitation intervention reduced the combined prevalence of 12 bacterial and protozoan enteric pathogens (the prespecified primary outcome), the individual prevalence of any single bacterial, protozoan, soil-transmitted helminth (STH), or viral pathogen, or the period prevalence of caregiver-reported diarrhoea 12 and 24 months postintervention.^34^ However, exploratory analyses indicated the intervention may have been protective against bacterial and STH infections among the cohort who were born into the intervention and may have reduced the spread of some pathogens into latrine entrance soils.

#### Long-term cross-sectional follow-up study

We are revisiting MapSan trial compounds at least 5 years after the sanitation intervention to conduct a cross-sectional survey of children who were born after the intervention was implemented. Due to substantial population turnover,^34^ both intervention and control compounds are being identified using previously collected geolocation data and their locations confirmed by study staff during site identification visits. Any compounds identified during the course of these mapping efforts that have received the sanitation intervention at least 5 years prior (built by WSUP to the same specifications) or match the original enrolment criteria for MapSan control compounds are also invited to participate, irrespective of previous participation in the MapSan trial. As an existing intervention, neither staff nor participants can be blinded to intervention status. We anticipate enrolment to continue for approximately 1 year and are again enrolling intervention and control compounds concurrently to limit any differential effects of seasonality and other secular trends across the enrolment period.

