### Limitations

As an observational, cross-sectional evaluation of an existing intervention, this study faces a number of limitations that may impact the generalisability of our findings. By design, all of the study participants will have been born after the intervention was implemented in order to evaluate intervention impacts among individuals across a range of ages who have been exposed to intervention for their entire lives. However, there is potential for confounding bias in our estimates of the intervention impacts on child health, particularly concerning socioeconomic factors that may be associated with increased pathogen exposures. While non-randomised, the criteria for intervention and control compounds differed only by engineering considerations that we believe to be independent of the outcome. However, in the years since the intervention was implemented, the presence of the intervention itself may have influenced the desirability of the intervention sites and thus the socioeconomic status (SES) of their residents, particularly in light of the high population turnover previously observed after only 1–2 years. All analyses will be adjusted for a location-specific wealth index to account for potential differential SES between treatment arms,^104^ in addition to other prespecified covariates associated with enteric pathogen exposure that may plausibly be related to treatment status, but the possibility of unmeasured and insufficiently controlled confounding remains.

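### Compounds added during mapping enter the two arms by different tests, so the statement that selection differed only on engineering grounds is supported for the original MapSan compounds but not for these

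*Protocol article*

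**What the plan says.** All places are in the protocol article.

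- **Original selection** (Original controlled before-and-after study). "WSUP selected intervention compounds using the following criteria", followed by a list of eight. The first is that "residents shared sanitation in poor condition as determined by an engineer". The others used for controls are at least 12 residents (3), willingness to contribute to construction costs (4) and legal piped water (7). "Control compounds were selected according to criteria 1, 3, 4 and 7 from the 11 neighbourhoods where the intervention was implemented" and from five further neighbourhoods.
- **Added intervention compounds** (Long-term cross-sectional follow-up study). The route admits compounds "that have received the sanitation intervention at least 5 years prior (built by WSUP to the same specifications"). No other compound-level criterion is given.
- **Added control compounds** (same section). These are compounds that "match the original enrolment criteria for MapSan control compounds are also invited to participate, irrespective of previous participation in the MapSan trial". The Eligibility criteria section repeats both routes, with past receipt for intervention compounds and present fulfilment of the criteria for controls.
- **WSUP sites outside the programme** (Urban sanitation intervention). "WSUP also constructed facilities to the same specifications at other compounds in the neighbourhoods prior to 2015", and building continued after 2016. How those sites were chosen is not stated.
- **Present condition in the analysis** (Independently upgraded controls). Children in upgraded control compounds are left out of the main analyses. Two further analyses count them as control and then as intervention. Intervention compounds are kept whatever the state of their facility.
- **Comparability** (Limitations). "the criteria for intervention and control compounds differed only by engineering considerations that we believe to be independent of the outcome".

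**The concern.** In the original trial, intervention compounds had to have poor shared sanitation before construction, and controls were chosen for the same trial on four of the same eight criteria. A control first found during mapping in 2022 or later can, it appears, be judged only on its state at that time. At least three of its four criteria can change over the years: sanitation condition, number of residents and willingness to pay. An added intervention compound is tested on a past event that later change cannot undo.

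Added controls would then be compounds that still have poor sanitation and still hold 12 or more people. A compound that was eligible in 2015, stayed outside MapSan and has since upgraded would never be enrolled. If persistently poor, crowded compounds carry more enteric pathogens, the control prevalence is raised and the intervention looks more protective than it is. This bears on the primary pooled effect, for which the article expects a smaller detectable effect than for single pathogens, so a modest bias matters more there.

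**Working it through.** **1. The plan's own figure.** The nearest checkable figure is the baseline prevalence at which a 25% reduction has 80% power: 34% (maximal scenario) to 46% (conservative). With K compounds per arm, m children per compound, between-compound variance 0.05 and a two-sided 5% test:

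Var = [2 × 0.05 + (p1(1−p1) + p2(1−p2))/m] / K

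- Conservative, K = 200, m = 2, 0.46 against 0.345: Var = (0.1 + 0.4744/2)/200 = 0.001686, SE = 0.0411, 0.115/0.0411 = 2.80, power 0.80.
- Maximal, K = 300, m = 2.5, 0.34 against 0.255: Var = (0.1 + 0.4144/2.5)/300 = 0.000886, SE = 0.0298, 0.085/0.0298 = 2.86, power 0.81.

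The figure reproduces. The issue here is selection, not arithmetic, but 25% gives a scale for judging the bias.

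**2. Entry tests side by side.**

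| Compound | Test | State tested |
|---|---|---|
| Original intervention | Criteria 1 to 8 | Before construction |
| Original control | Criteria 1, 3, 4, 7 | Original trial |
| Added intervention | WSUP facility at least 5 years ago | Past event |
| Added control | Criteria 1, 3, 4, 7 | Apparently at follow-up |

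The first two rows fit the Limitations sentence. The last two do not.

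**3. What the planned analyses can recover.** Recoding upgraded controls as control or as intervention works only on enrolled children. It cannot bring back a compound outside MapSan that failed criterion 1 at mapping because it had upgraded. The stated adjustment set (age, sex, caregiver education, wealth) does not contain compound source.

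**4. How many could be added.** The article gives 408 compounds at 24 months but no split by arm. Assume 204 per arm, all re-enrolled:

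- 200 per arm: none needed.
- 220 per arm: 16/220 = 7%.
- 300 per arm: 96/300 = 32%.

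These are power scenarios, not recruitment targets.

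**5. Size of the bias.** Let f be the share of control children from added compounds and r their prevalence relative to properly comparable controls. A true prevalence ratio of 1 appears as 1/((1−f) + f × r). The values of r are assumptions.

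| f | r = 0.9 | r = 1.1 | r = 1.25 | r = 1.5 |
|---|---|---|---|---|
| 0.07 | 1.01 | 0.99 | 0.98 | 0.97 |
| 0.32 | 1.03 | 0.97 | 0.93 | 0.86 |

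**6. Upgrading alone.** Assume 20% of controls eligible in 2015 have upgraded, with prevalence 30% against 40% in the rest. Unselected prevalence is 0.8 × 40% + 0.2 × 30% = 38%, so r = 40/38 = 1.05. The formula gives about 0.996 at f = 0.07 and 0.983 at f = 0.32.

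The main analysis drops upgraded controls from every source. In this example, original and added controls would then both stand at 40%, and the apparent ratio is 38/40 = 0.95 whatever f is. A restriction to original compounds therefore removes the shift only if upgraded controls are kept in.

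**The case against.** The case on the other side is substantial.

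- **Most compounds are from MapSan.** The article says so (Minimum detectable effect size), and the conservative scenario of 400 compounds lies below the 408 already seen. This stands and limits the size.
- **The timing is inferred.** The article does not say as of when the criteria are checked for added controls, and a fuller protocol may. This stands. Present-day checking is a strong inference from the tense used and from practicality, not a stated fact.
- **Dropping upgraded controls is open and is tested.** The article announces it and also counts them as controls. This stands for enrolled compounds, not for those that never entered.
- **The direction is not fixed.** Screening on willingness to pay and legal piped water could favour better-off controls and pull the other way. This stands.
- **The Limitations sentence is in the past tense, and the text after it concedes later change.** It does read most naturally as the original selection. The concession, however, concerns who came to live at the sites, with wealth adjustment as the answer, and not how added compounds were chosen.

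A reader might go further and infer that the arms as a whole were selected at different times and are not comparable, or that added intervention compounds were not screened at all. The documents do not support either reading. Original compounds in both arms were chosen for the same trial and are revisited. Silence on how WSUP chose its other sites does not show that it applied no criteria.

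**Conclusion.** The concern holds for compounds added during mapping and, separately, for the one-sided filter on present condition in the main analysis. The entry tests differ by arm, the comparability sentence is not supported for added compounds, and no analysis described in the article isolates the effect.

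The bias is of unknown size and direction, plausibly towards a protective effect. If few compounds are added, their contribution is small: about 0.98 to 1.00 in place of 1 in the upgrading example, against detectable reductions of 25% for single pathogens. It reaches 0.86 only if about a third of control children come from added compounds with 1.5 times the prevalence. All of this rests on an even split of the 408 compounds, full re-enrolment and assumed prevalences. The conclusion is that comparability is unsupported for part of the sample, not that the arms are shown to be non-comparable.

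**What to change.** 1. Record for each compound whether it was in the original MapSan trial or newly added, and report the numbers by arm.
2. Prespecify a sensitivity analysis of the primary and secondary outcomes restricted to original MapSan compounds, with independently upgraded controls kept in the control arm.
3. Limit the comparability sentence in Limitations to original MapSan compounds, and name the different entry rules for added compounds as a limitation.

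Two other remedies are not advised. Current compound size should not join the primary adjustment set, because the intervention may have affected it: the article itself says the intervention may have changed the desirability of the sites. Compound leaders' recall of 2015–2016 should not be relied on, given the turnover that the article reports.

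The cost is analysis-plan wording, one recorded variable and wider intervals in the restricted analysis. No extra enrolment is needed. With 204 compounds per arm (the even-split assumption) and the same number of children per compound, intervals widen by a factor of about √(220/204) = 1.04 in the moderate scenario and √(300/204) = 1.21 in the maximal one.
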